
**2.3.2. Environment**

Each of the study key personnel comes from an academic setting with extensive experience in the design, conduct, and analysis of longitudinal studies of child health. The Department of Population Medicine at Harvard Medical School and Harvard Pilgrim Health Care is internationally recognized for its influential research in population health, including studies of the lifecourse influences on later health and disease risk. Bristol’s School of Social and Community Medicine demonstrates similar excellence in epidemiological research, including in early-life risk factors for chronic disease. In the 2008 UK Research Assessment Exercise, 70% of the School’s epidemiology research was rated as world leading/internationally excellent. The School houses the MRC Centre for Causal Analyses in Translational Epidemiology, which will be available to provide methodological expertise, and the Avon Longitudinal Study of Parents and Children (ALSPAC) which has provided Drs. [name], [name] and [name] with enormous experience of detailed phenotyping in large-scale prospective birth cohorts.

**2.3.3. The PROBIT study**

**a. Study Population**

Thirty-four maternity hospitals and one each of their affiliated polyclinics (the clinics where children are followed for routine health care) were randomly assigned to receive a breastfeeding promotion intervention (experimental group) or to continue the prevailing maternity hospital and polyclinic practices at the time of randomization (control group). Cluster randomization was preferred over individual randomization because randomizing individual women within the same maternity hospital to different interventions would probably have led to contamination and a dilution of the effect of the intervention. After randomization, two hospitals from two different pairs refused to participate and a third randomized site was removed from the trial because of documented falsification of outcome data.^139^ This left 16 intervention and 15 control sites in the trial.

| ***Table 1: Baseline comparison of mothers and infants enrolled in the PROBIT Trial*** | | |
| --- | --- | --- |
| **Variable** | **Control (n=8181)** | **Experimental (n=8865)** |
| Maternal age 20-34 (%) | 82.3 | 81.4 |
| University education (%) | 13.0 | 14.1 |
| No other children in the household (%) | 56.1 | 59.8 |
| Gestational age (weeks) | 39.3 | 39.4 |
| Birth weight (g) | 3446 | 3448 |
| Birth length (cm) | 52.2 | 51.9 |
| Birth head circumference (cm) | 34.8 | 35.1 |
| Apgar score at 5 minutes (%) | 8.5 | 8.6 |
| Male sex (%) | 51.6 | 51.8 |

Recruitment for PROBIT began in June 1996 and continued until the end of December 1997. Mothers were eligible for participation if they initiated breastfeeding on admission to the postpartum ward, had no illnesses that would contraindicate breastfeeding or severely compromise its success, and had given birth to a healthy singleton infant of 37 weeks or more gestation, 2500 g or more birth weight, and Apgar score 5 or higher at 5 minutes. Study staff estimated that only 1-2% of eligible women declined participation. Since all women initiated breastfeeding, the experimental intervention was designed to increase the duration and exclusivity of breastfeeding. A total of 17,046 mothers (n=8865 intervention and n=8930 controls) had surviving infants. The randomization procedure produced groups with similar distributions of potentially confounding sociodemographic and clinical characteristics^21^ (**Table 1**)**.**

**b. The PROBIT Intervention**

***Table 2: The Ten Steps of the WHO’s Baby Friendly Hospital Initiative (BFHI).***

| 1 - | Maintain a written breastfeeding policy that is routinely communicated to all health care staff. |
| --- | --- |
| 2 - | Train all health care staff in skills necessary to implement this policy. |
| 3 - | Inform all pregnant women about the benefits and management of breastfeeding. |
| 4 - | Help mothers initiate breastfeeding within one hour of birth. |
| 5 - | Show mothers how to breastfeed and maintain lactation, even if they are separated from their infants. |
| 6 - | Give infants no food or drink other than breastmilk, unless medically indicated. |
| 7 - | Practice “rooming in”-- allow mothers and infants to remain together 24 hours a day. |
| 8 - | Encourage unrestricted breastfeeding. |
| 9 - | Give no pacifiers or artificial nipples to breastfeeding infants. |
| 10- | Foster the establishment of breastfeeding support groups and refer mothers to them on discharge. |

The experimental intervention included 10 steps that maternity hospitals must implement to become certified as ‘Baby Friendly’ (**Table 2**).^140^ Participants, usually the chief obstetrician and pediatrician from each of the intervention maternity hospitals and polyclinics, respectively, received the 18-hour Baby Friendly Hospital Initiative (BFHI) lactation management training course, which was organized by the European Regional Office of the WHO. The course emphasized methods to maintain lactation, promote exclusive and prolonged breastfeeding, and resolve common problems. Full implementation of the experimental intervention required 12 to 16 months to train all midwives, nurses, and physicians providing care to study mothers and infants during labor, delivery, and the postpartum hospital stay, and all pediatricians and nurses working at the polyclinics. Monitoring visits were conducted before and during recruitment and follow-up to ensure compliance with and maintenance of the study protocols.

**c. Data collection and validation at enrollment and in infancy**

Sociodemographic and clinical information was recorded on an enrollment form completed during the postpartum stay. In Belarus, infants are seen monthly for routine well-child visits and whenever they are ill. Classification of the degree of breastfeeding was based on WHO definitions.^140^ An infant was considered to be exclusively breastfed at three months if the feeding information obtained at one, two, and three months indicated that he or she was being breastfed and that no solids, non-breast milk, or water or other liquids (other than vitamins or medications) were being administered to the infant. An infant was considered to be exclusively breastfed at 6 months if, in addition to the above criteria, he or she was not receiving any other liquid or solid foods at the 6-month visit. An infant was considered to be predominantly breastfed if he or she received no solids or non-breast milk; juices, water, teas, and other liquids were permitted in this category.

Because the clinical outcomes were measured by the same pediatricians involved in implementing the experimental intervention or usual care, they could not be blinded to the intervention or control status of the study infants. A routine audit of data validity was therefore carried out at each study site. Twenty polyclinic charts were selected at random and the data on breastfeeding and infant outcomes at three months were compared with the data on these outcomes recorded on the PROBIT polyclinic visit forms. Of the 20 audited polyclinic charts, maternal interviews were also carried out for 10. For breastfeeding at three months, agreement was considered present if the date of weaning in the polyclinic chart or by maternal interview was within 15 days of the date recorded on the PROBIT polyclinic visit forms. For continued breastfeeding at three months, the kappa values for maternal interviews were 0.89 (95% CI: 0.81-0.97) in the experimental group and 0.94 (0.89-0.99) in the control group. Information about the outcome data collected at each PROBIT follow-up visit is summarized in **Table 3** and detailed below.

| ***Table 3. Visit schedule and previous funding for the PROBIT studies*** | | | |
| --- | --- | --- | --- |
| **PROBIT phase** | **Funding source** | **PI** | **Funded components** |
| PROBIT I  (Infant follow-up through 1 year) | Canadian Institutes of Health Research | [name] | Baseline characteristics at enrollment  Infant growth, infectious diseases, and atopic eczema |
| PROBIT II  (Child follow-up through 6.5 years) | Canadian Institutes of Health Research | [name] | Child adiposity, asthma, allergy, dental caries, intelligence & behavior |
| PROBIT III  (Child follow-up through 11.5 years) | Canadian Institutes of Health Research | [name] | Child adiposity and blood pressure |
|  | European Union (EARNEST Project) | [name] | Biomarkers of growth and heart disease risk in children (IGF-I, insulin, glucose, apoA1, apoB) |
|  | NICHD (R01 HD050758) | [name] | Child adiponectin and child metabolic syndrome |
| ***PROBIT IV*** | ***Current proposal*** | ***[name] & [name]*** | ***Child cognition, vision, atopic eczema, lung function, adiposity measures and blood pressure*** |

**d. Outcomes in infancy (PROBIT I)**

The first phase of follow-up (PROBIT I) assessed intervention effects on: breastfeeding duration/exclusivity; gastrointestinal and respiratory infection; and atopic eczema among infants.^21^ As seen in **Figure 1**, infants from intervention sites were 7 times more likely to be exclusively breastfed at 3 months (43.3% vs. 6.4%; P<0.001) and 13 times more likely at 6 months (7.9% vs. 0.6%; P = 0.01). Nearly twice as many intervention women were predominantly breastfeeding at 3 months (51.9 vs. 28.3%, p < 0.05) and nearly 7 times as many at 6 months (10.6% vs. 1.6%; P = 0.003). These differences were large enough to cause an appreciable reduction in gastrointestinal tract infections (9.1% vs. 13.2%) and atopic eczema (3.3% vs. 6.3%).

**e. Outcomes at age 6.5 years (PROBIT II)**

In PROBIT II, associations of breastfeeding promotion with child outcomes, including atopic disease, cognitive development, behavior, growth, obesity and blood pressure, were investigated. When the children were approximately 6.5 years of age, pediatricians invited them to the polyclinics for a study visit lasting about 1.5 hours. The participation rate was 13,889 (85%) of the 16,442 followed-up at 12 months (82% of the original cohort of 17,046). Outcomes included atopy,^56^ behavior,^25^ growth and blood pressure,^23,113^ and dental caries.^24^ Results for the IQ and asthma outcomes are described in detail above (**Section 2.1.**).

**f. Outcomes at age 11 years (PROBIT III)**

***Table 4: Intra-class correlation coefficients (ICC) for measurements taken in PROBIT III***

| *Measurement* | *ICC* |
| --- | --- |
| Standing height | 0.03 |
| Sitting height | 0.03 |
| Weight | 0.02 |
| Bioimpedance | 0.01 |
| Mid-upper arm circumference | 0.03 |
| Systolic blood pressure | 0.12 |
| Waist circumference | 0.07 |
| Hip circumference | 0.03 |
| Head circumference | 0.10 |
| Triceps skinfold thickness | 0.12 |
| Subscapular skinfold thickness | 0.04 |
| Glucose | 0.08 |

At 11.5 years (PROBIT III), we investigated effects of breastfeeding on growth and cardio-metabolic risk factors. Pediatricians performed anthropometric measurements on mothers and children, and collected fasting blood via fingerstick. We have completed all study visits and await final data entry and results of laboratory assays. The participation rate - 13,891 children were seen – attests to our ability to maintain excellent follow-up and thus minimize retention bias. Intra-class correlation coefficients were extremely low for all measured outcomes (**Table 4**), indicating valid measurements with a low degree of clustering.

In an interim intention-to-treat analysis (n = 12,374), cluster-adjusted mean differences in experimental vs. control groups were essentially null: 0.16kg/m^2^ (95% CI: -0.08, 0.40) for BMI; 0.43% (-0.15, 1.01) for body fat; 0.33cm (-1.25, 1.92) for waist circumference; 0.11mm (-1.53, 1.74) for triceps skinfold thickness; 0.62cm (-0.40, 1.64) for height; and 1.12mmHg (-1.06, 3.30) for systolic blood pressure.^141^ The odds ratio for obesity (experimental vs. control arms) was 1.19 (0.95, 1.50). We found similar null results for maternal postpartum adiposity.^142^ We now have a number of papers in progress presenting results of the intention-to-treat analysis of the anthropometric and biochemical study outcomes. Our joint experience leading PROBIT III yields several important messages: we have demonstrated our successful collaboration in leading a PROBIT outcome visit; we achieved high rates of follow-up with little evidence for bias in follow-up or clustering in outcome assessments; and we require 4 years of funding to allow for complete data collection and analysis.

**g. Summary**

The PROBIT intervention successfully improved the duration of total and exclusive breastfeeding in a large population of mothers and infants. Participant characteristics were evenly balanced at study enrolment, suggesting that randomization was successful and confounding by measured and unmeasured characteristics is unlikely. At every phase of follow-up (I, II & III), those followed up (> 80%) had similar baseline characteristics *vs.* non-responders, providing reassurance against follow-up bias. Data collection through 11.5 years suggests high follow-up rates and uniform, high-quality outcome data, minimizing the likelihood of bias. The experienced and productive team will build upon established relationships to accomplish the proposed aims of this project.

**2.3.4. PROBIT IV (current proposal)**

**a. Eligible population**

We will attempt to follow-up all participants enrolled in PROBIT I, most of whom were seen at age 11.5 years (PROBIT III). Follow-up will commence in June 2012 when the oldest child will be 16 years. We will “front load” recruitment so that virtually all children are evaluated as near as possible to their 15^th^ birthday and as few children as possible will be of school-leaving age (17 years). We again plan to follow up 14,000 children (82% of the original cohort). Given 97% follow-up in PROBIT I and 82% follow-up in both PROBIT II and III, we feel this goal is achievable; furthermore, the follow-up protocol will be shorter (1 vs. 2 hrs) and does not involve fasting or blood sampling, so will be more convenient for both children and clinicians; and we have recently updated contact information on the large majority of children seen between 2008-2010 for PROBIT III. Emigration levels are low and few families move their residence, except within Minsk. However, it is critical that we begin data collection soon, as after age 17 many children leave home to attend university, and we may lose the opportunity for further contact.

**b. New data**

As in PROBIT I-III, polyclinic pediatricians will locate and invite children to attend the follow up clinic examination where the pediatricians will collect the measures described below.

***Informed consent****.* As we have done at each stage of data collection, pediatricians will obtain verbal informed consent via telephone or written informed consent from a parent for each participating child. They will also obtain verbal assent from children. Belarusian law disallows minors from providing written informed consent.

***Neurocognitive function.***  Cognition will be assessed using the *Mindstreams* Global Assessment Battery (NeuroTrax Corp), a software package that is installed onto PCs and contains a validated computerized cognitive battery with multiple domains.^143-145^ After detailed review of available instruments, we chose *Mindstreams* because it tests a breadth of cognitive function; is brief (≈ 45 mins); includes a verbal domain (the domain most strongly associated with breastfeeding in PROBIT II); is self-administered; has an available, validated Russian language version; requires little computer literacy (only mouse clicks and number pad entries); and includes built-in trial tests with feedback before starting, to ensure comprehension. Other available tests are longer (> 1 hour); do not include verbal ability or have existing verbal tests that may not be generalizable to Russian; or are administered by trained personnel, so are not practical/cost-effective in our large trial. The *Mindstreams* non-verbal ability domain tests reaction time, immediate and delayed non-verbal memory (geometric figures), motor skills (e.g. hand-eye coordination; spatial recognition) and visual-spatial processing. The verbal ability domain tests immediate and delayed verbal memory (words; pictures) and word recognition. Aggregate outcome parameters will be computed from raw data using automatic algorithms, blind to intervention, standardized by age and fitted to an IQ-style scale (mean 100, SD 15). Standardized parameters that measure similar cognitive functions will be averaged to produce 7 ‘index scores’, each summarizing performance in a single domain:^146^ memory; executive function; visual-spatial perception; verbal function; attention; information processing; and motor skills. A global cognitive score, reflecting general cognitive status, will be computed as the average of the index scores.

***Vision****.* We will use the LogMAR-Crowded test (<http://www.keeler.co.uk>) to measure vision without optical correction, visual acuity with optical correction (if present) and pinhole acuity in each eye, to determine if any deficit in vision is refractive. A vision cut-off (LogMAR 0.2, equivalent to worse than 6/9 Snellen acuity) will be used to define myopia; this threshold has high sensitivity (>90%) and specificity in identifying myopia,^126,147^ and that 91% of those with this level of vision at 16 years will be myopic in later life.^148^ The definition of myopia will be validated in a subset of children from the largest polyclinic (n=1000) using open field auto-refraction with a distant fixation target (Maltese cross at 5 meters) to stabilize accommodation without need for pharmaceutical cycloplegia (which could otherwise compromise participation).

***Atopic eczema.*** We will identify cases of atopic eczema through physical skin examinations conducted by the PROBIT study pediatricians, and collect additional data on eczema symptoms and skin health through questions from the International Study of Allergy and Asthma in Children (ISAAC) questionnaire. Study pediatricians will examine PROBIT participants for signs of flexural dermatitis around the eyes, the back of the neck, the front of the elbows, the back of the knees, and the front of the ankles. Evidence of flexural dermatitis upon exam at any of the 5 examination sites is sufficient for a diagnosis of atopic eczema.

***Lung function****.* We will measure peak expiratory flow rate (PEFR), forced expiratory volume in one second (FEV_1_), forced vital capacity (FVC), and FEV_1_/FVC ratio using the ‘Micro spirometer Plus’ (Micromedical, [www.micromedical.co.uk](http://www.micromedical.co.uk)), which meets American Thoracic Society (ATS) and European Respiratory Society (ERS) criteria.^149^ ATS/ERS guidelines will be followed in performing the measures and assessing acceptability and reproducibility.^150^ Room temperature and barometric pressure will be recorded. Children will be asked to complete the maneuver 5 times and the results and technical acceptability (i.e. maximum inspiration, a good start, a smooth continuous exhalation and maximal effort)^150^ of each blow recorded. We will aim for 3 acceptable and 2 repeatable (two largest values of FVC/FEV_1_ within 0.15 liters of each other) maneuvers.^150^ Pediatricians will also measure child height using existing PROBIT stadiometers as they have done previously.^23^ The child will self-complete the European Community Respiratory Health Study questionnaire,^151^ which includes measures of respiratory symptoms, self-reported asthma/allergy, smoking, indoor exposures and asthma treatment.

***Adiposity and blood pressure.*** Systolic and diastolic blood pressure readings will be measured using the semi-automated oscillometric Omron 705IT; (Omron Health Care, UK) using appropriate cuff size. The time of taking the measurement and room temperature (measured with an electronic thermometer) will be recorded. Standing height will be measured in duplicate (and averaged) using a wall-mounted. Waist circumference will be measured in duplicate at the mid-point between the iliac crest and the lower edge of the ribs in the mid-axillary line using a nonstretchable cloth tape measure. The Tanita TBF 300 GS body-fat analyzer (Tanita Corp, Tokyo, Japan) will be used to measure leg-to-leg bioimpedance from which weight, percent body fat, fat mass, and fat free mass are calculated.

**c. Training of pediatricians**

To ensure that high quality data are collected and that repeatable measurements can be obtained, we will hold a training workshop prior to starting fieldwork (as we have done in all past follow-ups). We will re-certify pediatricians in height measurement and certify them in the spirometry, cognitive and vision measures. Spirometry training will include an instruction session ([name]), followed by practical sessions to assess each pediatrician’s coaching technique and data outputs, with individual feedback. As we have done in the past (e.g. in PROBIT II for IQ) we will practice spirometry on consenting local children who are not study participants. Training for the cognitive function test will be minimal as the pediatricians only need to provide standardized, simple instructions to the children regarding how to execute the test from the software. [name] will advise on administering the cognitive function test and related analyses. [name] will provide training in conducting the skin examinations, followed by a written, skills-based test to confirm that the pediatricians can accurately identify signs of flexural dermatitis. [name] will provide training in vision assessment, by lecture with follow-on practical and individual feedback. Subsequent workshops will be held 6 monthly to monitor follow-up, clarify procedures and re-standardize measurements.

**d. Quality control**

*Monitoring.* Once the data collection process is underway, we will initiate data monitoring visits to each polyclinic. Trained Belarusian monitors will observe pediatricians and repeat key measurements during study visits on one full day.

*Auditing.* Once data collection is complete at each polyclinic, we will schedule auditing visits in order to assess the inter-observer reproducibility, an important step given that the pediatricians are not blinded to randomization status.^23^ The Belarusian auditors (likely the same individuals who will serve as monitors) will conduct duplicate (repeat) visits on a subset of randomly chosen PROBIT IV participants. We will perform 4 audit visits at each polyclinic with a single pediatrician, and a total of 6 audit visits (3 per pediatrician) for each polyclinic with two pediatricians. The auditors will be blinded to the initial measurements. We will calculate correlation coefficients with 95% confidence intervals for the initial vs. repeat measurements.

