**2.1.1. Neurocognitive function**

Brain development is fastest in the 3^rd^ trimester of gestation and the first 4 years after birth^11^ and is influenced by nutrition.^12-15^ Observational studies report consistently higher intelligence quotient (IQ) scores of 2 to 5 points in breast- *vs* formula-fed term infants.^16^ However, although many observational studies control for socioeconomic status and maternal intelligence, uncontrolled confounding by subtle differences in the mother’s behavior or her interaction with the infant are possible. In the 6.5 year follow-up of PROBIT, IQ was measured by the Wechsler Abbreviated Scales of Intelligence (WASI).^17^ Children randomized to the breastfeeding promotion arm had a 7.5 (95% CI: 0.8 to 14.3) point advantage in verbal IQ, 2.9 (-3.3 to 9.1) point difference for performance IQ and 5.9 (-1.0 to 12.8) point difference for full-scale IQ, *vs* controls.^17^ Smaller, but consistently positive, differences of 2 to 3 IQ points were seen in a blinded audit of 190 children and blinded teacher rated academic performance. Our experimental data, based on strict randomization and intention-to-treat analysis, is therefore consistent with observational data^16^ and suggests that associations in term infants are causal.^17,18^

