Nevertheless, these findings have been controversial and merit further investigation. Our current proposal maintains the strengths of earlier work within PROBIT, i.e. the large sample size and randomized design, while improving on the prior limitations, namely the young age at outcome assessment and imprecisely measured outcomes. An observational study and meta-analysis^19^ found that a positive association of breastfeeding with child IQ became negligible after controlling for parental IQ. Other studies that controlled for maternal IQ, however, report persistent, albeit attenuated, IQ benefits.^16,20^ In an RCT like PROBIT, parental IQ should be distributed randomly between treatment groups, as demonstrated for other measured baseline characteristics,^21^ and thus should not confound the intervention effect. The effect sizes for IQ at age 6.5 in PROBIT were imprecisely measured, due to high within-pediatrician clustering of IQ values across the 31 trial sites.^22^ While analyses based on the blinded audit and teacher ratings suggest the direction of the observed differences is robust, we do not know whether the large difference in verbal IQ arose by chance or a systematic overestimate of verbal IQ in the experimental group. The smaller differences seen in the blinded audit and teacher ratings may more closely estimate the true effect. All pediatricians were trained, monitored, and audited in their administration of the WASI, and no beneficial intervention effects were observed for other outcomes,^23-25^ equally subject to systematic error, providing some reassurance that the pediatricians’ assessments of outcomes were unbiased. Nevertheless, the pediatricians who administered the WASI were not blinded to the trial arm of the children they examined, as many had contributed to the original intervention by providing postnatal support and encouragement of prolonged, exclusive breastfeeding.^21^ It is possible that the pediatricians at the intervention sites may have differentially administered or scored the WASI. In addition, about 20% of children seen at age 6.5 years had yet to start school, and they may have had difficulty completing the IQ test, potentially generating random measurement error.

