We will minimize potential bias in outcome assessment by using self-administered, computer-scored measures of cognitive function. Although the polyclinic pediatricians cannot not be blinded to the intervention or control status, the pattern of results in previous phases of PROBIT follow-up (i.e. no effect seen for respiratory infections in infancy or child adiposity^21,23^), do not suggest systematic bias towards better outcomes in the intervention group. The duplicate audit visits will provide additional evidence against bias due to non-blinding. Losses to follow up and incomplete data are potential sources of bias. We expect similar high rates of follow-up as we achieved in PROBIT III. We will be able to compare and account for characteristics at baseline and at earlier follow-up visits between children who do and do not present for assessment at age 15-16. Compared with observational cohorts, registered trials are less prone to problems of selective submission and publication bias. Generalizability is a concern. As the study is in Belarus, all participants are white. However, PROBIT includes an economically diverse population, and fewer than 2% of eligible mothers refused initial participation in the study. Belarus resembles Western developed countries in both basic health services and sanitary conditions. An uncontaminated water supply is ensured and monitored throughout the Republic by public health authorities, and clinics and physicians are abundant and readily accessible, even in rural areas. Therefore, we believe it will be reasonable to generalize results to children in the US.

This proposal represents good value. Previous grants have already supported recruitment, collection of baseline characteristics, and delivery of the intervention. As detailed in the budgets, the Canadian Institutes of Health Research will provide substantial co-funding (~$1.2m). We require funding only for the collection and analysis of outcome measures. In addition to the proposed aims, great potential exists for the conduct of other epidemiologic research based on earlier follow-ups and stored blood, including genetic analyses.

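### The audit's only named analysis, correlation coefficients with no comparison by arm, does not support the claim that the audit gives evidence against non-blinding bias

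*Protocol*

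**What the plan says.** Protocol 2.3.4 d (Quality control, Auditing) says the audit visits are there to "assess the inter-observer reproducibility, an important step given that the pediatricians are not blinded to randomization status". Each polyclinic gets 4 audit visits if it has one pediatrician and 6 if it has two. The auditors are blinded to the first measurements; blinding to arm is not mentioned. The only analysis named is this: "We will calculate correlation coefficients with 95% confidence intervals for the initial vs. repeat measurements".

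Protocol 2.3.8 (Strengths and limitations) accepts that the pediatricians cannot be blinded. It says earlier results "do not suggest systematic bias towards better outcomes in the intervention group" and continues: "The duplicate audit visits will provide additional evidence against bias due to non-blinding".

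Protocol 2.1.1 describes the same threat for IQ at age 6.5. The investigators do not know whether the large verbal IQ difference "arose by chance or a systematic overestimate of verbal IQ in the experimental group", and they add: "It is possible that the pediatricians at the intervention sites may have differentially administered or scored the WASI". That section also reports that "differences of 2 to 3 IQ points were seen in a blinded audit of 190 children", so the earlier audit was read through the difference between arms.

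**The concern.** In both 2.1.1 and 2.3.8 the bias to be ruled out has a direction: measurements in one arm are pushed towards better values. A correlation describes how well two sets of values rank and scale together. It does not describe whether one set lies higher than the other, and the plan does not compare the arms. A high correlation would be expected with or without the bias, yet section 2.3.8 would let it be quoted as reassurance.

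The stake is the credibility of outcomes that depend on the pediatrician's judgement or coaching: the skin examination for eczema, spirometry, visual acuity and waist circumference. No ITT estimate, test or sample size changes.

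**Working it through.** The protocol gives no figure for what the audit can detect, so there is none to reproduce.

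**Inputs**
- Audit size (2.3.4 d; 31 polyclinics, 16 intervention and 15 control, from 2.3.3 a): 31 × 4 = 124 if every site has one pediatrician, 31 × 6 = 186 if every site has two. The mix is not stated, so this is a range.
- Yardstick (2.3.6 and Table 5): standardized detectable ITT difference 0.1 SD; for FEV₁, SD 480 ml and 48 ml.
- Initial-to-repeat correlation r: not in the document. Assumed 0.8, range 0.7 to 0.9.

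**Model.** Initial = true + e₁ + b × arm; repeat = true + e₂. Each measurement has variance 1 and b is the shift in SD units. The arms are equal in size with no true effect.

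**1. Pearson correlation within an arm.** Corr(X + b, Y) = Corr(X, Y), so it stays at 0.80 for every b. In simulation (4,000 runs per setting, shifts of 0.1 and 0.5 SD), testing for a between-arm difference in correlation rejected in 4% to 5% of runs, which is the type I error rate.

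**2. Pearson correlation pooled over arms.** This equals r / √(1 + b²/4).
- b = 0.1: 0.8 / √1.0025 = 0.799
- b = 0.5: 0.8 / √1.0625 = 0.776

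The Fisher-z 95% interval with no shift is 0.726 to 0.856 (n = 124) or 0.741 to 0.846 (n = 186). Both values lie well inside.

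**3. Absolute-agreement ICC**, in case that is the coefficient intended: 2 cov / (var₁ + var₂ + squared mean difference).
- b = 0.5, pooled: 1.6 / (1.0625 + 1 + 0.0625) = 0.753
- b = 0.5, shifted arm only: 1.6 / (1 + 1 + 0.25) = 0.711 (simulation 0.713)
- b = 0.1, pooled: 1.6 / (1.0025 + 1 + 0.0025) = 0.798

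It responds to a large shift but hardly to a small one. Pooled, it does not show which arm moved.

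**4. Between-arm contrast in mean (initial minus audit), same data.** SE = √(2(1 − r)) × √(4/n).
- n = 124: √0.4 × √(4/124) = 0.114 SD; 95% half-width 1.96 × 0.114 = 0.22 SD
- n = 186: √0.4 × √(4/186) = 0.093 SD; half-width 0.18 SD

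The shift detectable with 80% power is (1.96 + 0.84) × SE = 0.32 SD (n = 124) or 0.26 SD (n = 186). For FEV₁ that is 153 ml or 125 ml, against 48 ml in Table 5. Over r = 0.7 to 0.9 the range is 0.39 to 0.18 SD. If the differences have an assumed ICC of 0.1, it is 0.44 to 0.225 SD.

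In simulation at r = 0.8, a 0.5 SD shift was found in 99% of runs (n = 124) or over 99.9% (n = 186). A 0.1 SD shift was found in 14% or 20%.

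**The case against.** The best defence is that the two sections are not explicitly joined. Section 2.3.4 d gives the aim as reproducibility, for which a correlation is a conventional if incomplete summary. Section 2.3.8 rests on the audit visits rather than on the coefficients, and offers them only as additional support. The team read its earlier audit through arm differences, and a statistical analysis plan could contain such a contrast. This narrows the point: the correlations do serve reproducibility. It does not remove it, because the protocol names one statistic, ties the audit to the lack of blinding, and states an inference which that statistic does not carry.

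Three stronger readings are tempting, and the documents do not support them.
- **That a correlation is blind to bias of any size.** This holds for a Pearson coefficient within an arm. Pooled, an r of 0.95 falls to 0.95 / √2 = 0.67 at a 2 SD shift, and an absolute-agreement ICC also falls. The type of coefficient is not specified.
- **That the age 6.5 IQ problem will recur unseen.** The cognitive test is now self-administered and computer-scored, blood pressure is semi-automated, and weight and body fat come from a bioimpedance analyzer. These are less exposed.
- **That 7.5 points against 2 to 3 measures the earlier bias.** The 7.5 is verbal IQ; full-scale was 5.9 and performance 2.9. The audit figure is given without a subscale or interval.

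**Conclusion.** The point stands in limited form: the analysis named in 2.3.4 d does not support the inference drawn in 2.3.8. At the assumed r of 0.8, a half-SD shift confined to one arm leaves a within-arm Pearson correlation unchanged and lowers the pooled one by 0.024, which 124 to 186 audits could not show.

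The audit data can do better, but only for gross bias. The arm contrast has 80% power for roughly 0.26 to 0.32 SD at r = 0.8, ignoring clustering. It cannot exclude a shift as small as the trial's 0.1 SD detectable difference. If auditors know the arm and share the bias, it cancels in the contrast too, and the protocol does not say whether they know.

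The sizes rest on the assumed r, a constant shift and normal errors; the qualitative conclusion holds over r = 0.7 to 0.9. This should be corrected, but it concerns a quality-control claim and not the primary analysis.

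**What to change.** - In 2.3.4 d, keep the reproducibility statistics but name them, preferably an absolute-agreement ICC or limits of agreement. For eczema, a yes/no finding, give kappa by arm.
- Add, for each pediatrician-measured continuous outcome, the between-arm contrast in mean (initial minus audit) with a cluster-adjusted 95% CI. Because audits follow completion of data collection at a site, include the time between the two visits as a covariate.
- State whether the auditors are blinded to arm as well as to the first measurements.
- Reword 2.3.8 so that any reassurance rests on that contrast and its interval. Say that it can reveal only gross bias and that a bias shared by auditors who know the arm would not show.

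The cost is a little more analysis and a more modest claim. No visits or data are added.
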